##### Qualitative research

We will also conduct a qualitative study based on the grounded theory to elucidate the meaning of the experiences of moxibustion treatment for KOA. Sixteen KOA patients who will be selected by convenience sampling will

be included in the qualitative study if they consent to give a recorded face-to-face interview. We will conduct individual in-depth interviews using open-ended questions at a site where they feel comfortable. The interviewer will ask the participants the key question, "Tell me about your experiences with obtain moxibustion treatment for treating KOA", and additional questions, such as "What is the most difficult activity due to KOA?", "Why did you choose moxibustion treatment? What was your motivation?", "What was your expectation when you participated?", "What types of changes did you feel after you received moxibustion? Were there any symptom changes after moxibustion treatment?", "Did you have any difficulties or problems during the moxibustion treatment? What did you do to overcome these troubles?", "Will you choose moxibustion treatment again when you have a similar or other symptom?", and "Will you recommend moxibustion treatment to others?". The data will be transcribed from the recording and analysed using the coding scheme, and researchers will then categorise them according to the process for qualitative research methods.

#### **Data and safety monitoring**

Regular monitoring that will be clarified in a standard operating procedure will be conducted at each site to ensure good data quality. Monitors will evaluate whether the case report forms are properly written and whether the recruiting and treatment procedures are adequately performed according to the protocol. Investigators from each site will be contacted to discuss whether it is necessary to revise the study protocol or inclusion criteria and other important issues. The investigators and independent researchers will assess the progress of the clinical trial and severe adverse events and determine whether they are acceptable and whether it will be necessary for the trial to be modified or stopped.

#### **Adverse events**

All unexpected and unintended responses that are not necessarily related to moxibustion treatment will be reported by the participants and practitioners at every visit. The adverse events known to occur following moxibustion treatment include blisters, redness, itching, burns, and respiratory symptoms. To avoid potential adverse events, the treatment day will be modulated within 3 days if the practitioner judges that the participant is not suitable for moxibustion treatment or the participant indicates moderate fatigue or an abnormal health condition.

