## Abstract

**Background:** The treatment of knee osteoarthritis, which is a major cause of disability among the elderly, is typically selected from multidisciplinary options, including complementary and alternative medicine. Moxibustion has been used in the treatment of knee osteoarthritis in Korea to reduce pain and improve physical activity. However, there is no sufficient evidence of its effectiveness, and it cannot therefore be widely recommended for treating knee osteoarthritis. We designed a randomised controlled clinical trial to evaluate the effectiveness, safety, cost-effectiveness, and qualitative characteristics of moxibustion treatment of knee osteoarthritis compared to usual care.

**Methods/designs:** This is a protocol for a multicentre, pragmatic, randomised, assessor-blinded, controlled, parallel-group study. A total of 212 participants will be assigned to the moxibustion group (n = 106) and the usual care group (n = 106) at 4 clinical research centres. The participants assigned to the moxibustion group will receive moxibustion treatment of the affected knee(s) at 6 standard acupuncture points (ST36, ST35, ST34, SP9, Ex-LE04, and SP10) 3 times per week for 4 weeks (a total of 12 sessions). Participants in the usual care group will not receive moxibustion treatment during the study period. Follow-up will be performed on the 5th and 13th weeks after random allocation. Both groups will be allowed to use any type of treatment, including surgery, conventional medication, physical treatment, acupuncture, herbal medicine, over-the-counter drugs, and other active treatments. Educational material that explains knee osteoarthritis, the current management options, and self-exercise will be provided to each group. The global scale of the Korean Western Ontario and McMaster Osteoarthritis Index (K-WOMAC) will be the primary outcome measurement used in this study. Other subscales (pain, stiffness, and function) of the K-WOMAC, the Short-Form 36v2 Health Survey, the Beck Depression Inventory, the Physical Function test, Patient Global Assessment, and the Pain Numerical Rating Scale will be used as outcome variables to evaluate the effectiveness of moxibustion. Safety will be assessed at every visit. In addition, an economic evaluation and a qualitative study will be conducted as a mixed-methods approach.

**Discussion:** This trial may contribute to developing evidence for the effectiveness and safety of moxibustion for treating knee osteoarthritis.

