## Methods/design

### Objective

The aims of this study are as follows: (1) to assess the effectiveness of moxibustion treatment for treating KOA on the occurrence of pain, function, depression, quality of life, and adverse events compared to usual care and (2) to assess the cost-effectiveness and cost-utility of moxibustion in addition to usual care in the treatment of KOA patients and explore how KOA patients experience moxibustion in Korea.

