### Intervention

#### Moxibustion treatment

Moxibustion treatment will be performed by DKMs who are certified by the Korean Ministry of Health and Welfare. They will have at least 2 years of clinical experience and will have received more than 6 years of oriental medicine college education. The treatment will be performed under the supervision of professors who specialise in acupuncture and moxibustion. All treatment regimens and outcome assessment methods will be standardised between the 4 centres, and basic information about this study and the monitoring process will be disseminated through workshops before the beginning of the study. This study is designed to evaluate moxibustion treatment as it is used in

normal practice. The practitioner will therefore be allowed to maintain a patient-practitioner relationship similar to a normal clinical situation. There will be no restrictions in the careful observation and questioning of participants.

In the moxibustion group, 3 moxibustion sessions per week will be performed during a 4-week period for a total of 12 sessions. The treatment will be conducted after sterilising the skin surface at the acupuncture points with the participant lying in a supine position at a room temperature of 22°C to 28°C. After the top of the moxibustion is sufficiently combusted without attachment to the points for approximately 5 to 10 seconds, the moxibustion will be attached at each point. When a participant believes that their heat tolerance has reached its maximum, the practitioners will place a new moxibustion at the same point. However, to prevent burns, the attached point can be changed to within a 1 cm diameter according to the discretion of the practitioners. A total of 3 moxibustions will be attached at each point at every visit. We will use smokeless indirect moxibustions made of mugwort with a paper cylinder (Manina, Haitnim Co., Korea) (Figure 2). This moxibustion has an adhesive on the bottom that can be used to attach it to the skin, and its effect lasts approximately 5 to 10 minutes. The expected total time of each treatment session will be 20 to 30 minutes. The treatment points were selected in a consensus process by professors and researchers who have an acupuncture and moxibustion specialist license in Korea based on a text book [24], literature reviews [12,14,25],

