### Sample size

We calculated the sample size according to our previous pilot study. A 2-sided 5% significance level and 80% power were considered to detect a mean difference in the WOMAC of -6.65 with a standard deviation (SD) of 15.4. Approximately 84 participants in each group were calculated to be required. Assuming a dropout rate of 20%, the sample size will be  $n = 106$  for each group (total  $n = 212$ ). A total of 32 participants will be assigned at the Korea Institute of Oriental Medicine (Daejeon University Hospital), and the remaining 180 participants will be equally assigned at the other 3 study hospitals. To recruit this number of participants, a 6-month study period is anticipated based on our pilot study.

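### The adverse-event reporting rule covers only unexpected responses, yet the next sentence lists known reactions to moxibustion as adverse events; the two need reconciling

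*Protocol*

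**What the plan says.** The protocol deals with event reporting in a short section headed Adverse events. Its first sentence is the reporting rule: "All unexpected and unintended responses that are not necessarily related to moxibustion treatment will be reported by the participants and practitioners", at every visit. Its second sentence reads: "The adverse events known to occur following moxibustion treatment include blisters, redness, itching, burns, and respiratory symptoms".

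Four other parts of the protocol bear on safety:

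- **Objective.** Aim 1 is to assess moxibustion "on the occurrence of pain, function, depression, quality of life, and adverse events compared to usual care".
- **Abstract.** "Safety will be assessed at every visit".
- **Table 1.** A Safety Assessment row marks the visits at which safety is assessed in each group, without defining what is assessed.
- **Moxibustion treatment.** Burns are foreseen in the procedure: "However, to prevent burns, the attached point can be changed to within a 1 cm diameter".

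The Data and safety monitoring section adds that monitors check the case report forms and conduct against the protocol, and that severe adverse events are reviewed. It does not say what counts as an adverse event.

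**The concern.** The rule joins two conditions with *and*: a response must be unexpected as well as unintended. The five reactions in the second sentence are unintended but, being known, are not obviously unexpected. So the paragraph calls them adverse events while its own rule, taken literally, does not ask for them to be reported.

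Expectedness is usually an attribute assigned to an event once it has been recorded. Here it stands as a condition for recording it. That matters for three reasons.

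- The comparison of adverse events with usual care is part of aim 1, and these are the reactions that the protocol itself ties to the treatment.
- Practitioners are among those who report, and they know the allocation (Randomisation and allocation concealment). An ambiguous word is therefore left to unblinded judgement, separately at four centres.
- The loss cannot be repaired later. No analysis plan can recover an event that was never written down, so this belongs in the protocol and the case report form, not in a statistical analysis plan.

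**Working it through.** No figure in the protocol is in dispute. The check is a comparison of texts, plus one count from Table 1.

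**1. Apply the rule to the listed reactions.** Under the literal rule an event is reported if it is unexpected and unintended; relatedness is not required.

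| Reaction | Unintended? | Unexpected, if known reactions count as expected? | Reported under the literal rule? | Called an adverse event in the next sentence? |
|---|---|---|---|---|
| Blisters | Yes | No | No | Yes |
| Redness | Yes | No | No | Yes |
| Itching | Yes | No | No | Yes |
| Burns | Yes | No | No | Yes |
| Respiratory symptoms | Yes | No | No | Yes |

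The last two columns disagree in all five rows. The third column rests on one reading of *unexpected*; the other reading is taken up in the objection.

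**2. Look for a wider definition elsewhere.**

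- Abstract: says when safety is assessed, not which events count.
- Objective: makes adverse events part of the comparison but does not define them.
- Moxibustion treatment: includes a precaution against burns, which confirms that burns are anticipated.
- Table 1: schedules the assessment only.
- Data and safety monitoring: covers form checks and severe adverse events, with no definition.
- Participant protections and ethics: cites general ethical guidelines and Korean Good Clinical Practice, with no definition in the text.

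None of these brings expected reactions into the reporting rule.

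**3. Count the safety assessments by group.** In the Safety Assessment row of Table 1, visits 2, 14 and 15 are marked for both groups and visits 3 to 13 for the moxibustion group only.

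- Usual care: visits 2, 14 and 15 = 3 assessments.
- Moxibustion: 3 shared + 11 (visits 3 to 13) = 14 assessments.

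Two forces therefore act on the recorded moxibustion rate in opposite directions. A literal reading of the rule would lower the count of the listed reactions, while 14 assessments against 3 give more occasions on which any event can be recorded.

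**4. Can the loss be sized?** That would need the true rate of the listed reactions and the share of sites reading the rule literally. The protocol gives neither, so no number of lost events can be derived.

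**The case against.** The strongest reply is that the paragraph should be read as a whole. Under a heading about adverse events, the first sentence says that responses are reported and the second gives the ones to look for. The clause on relatedness widens the scope, which is not how one drafts a rule meant to screen events out. *Unexpected* may also refer to the individual participant: a burn that the procedure tries to prevent can be a known risk of the treatment and still not be expected in a given session. Regular form checks and the commitment to Good Clinical Practice make it less likely that a site would ignore a burn.

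Much of this stands. The authors very probably intended to record these reactions, and the wording is no evidence that they will go uncollected. What remains is that the rule admits two readings, the literal one leaves out reactions that the paragraph itself calls adverse events, and nothing else in the text tells a site or a monitor which reading applies.

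A reader might also infer that the listed reactions can occur only with moxibustion, so that the filter acts on one arm alone. The protocol does not support that. The Usual care section lets both groups use physical treatment, acupuncture and other active treatments, and redness, itching and respiratory symptoms are not specific to moxibustion. *Mainly in the moxibustion group* is as far as the text goes.

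**Conclusion.** The point holds as an internal inconsistency in the Adverse events section. Read literally, the reporting rule omits all five reactions that the next sentence names as adverse events, and no other section supplies a wider definition. The consequence is a risk of under-recording those reactions, mainly in the moxibustion group, and of different recording of the same harm across the four centres. This rests on the assumption that at least some sites would treat a reaction known to follow the treatment as expected.

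Two stronger conclusions are tempting and should not be drawn. The first is that the reported incidence of these reactions would fall to near zero; that would need every site to take the narrowest reading at every visit, and the protocol gives no rate or practice from which to judge this. The second is that the adverse-event comparison is biased towards showing moxibustion as safe. For the total adverse-event rate the net direction is unknown, because the unequal schedule of safety assessments (14 against 3) works the other way.

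The primary endpoint, the sample size and the effectiveness analysis are unaffected. The point still merits correction, because it touches a stated aim and must be settled before events are collected.

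**What to change.** Change the first sentence of the Adverse events section and add two short statements:

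- Replace the opening phrase that requires responses to be unexpected and unintended with: *All untoward medical occurrences in either group, expected or not, and whether or not related to moxibustion*. The existing clause on relatedness then becomes redundant and can go.
- State that the five effects listed in the second sentence are always recorded.
- State that expectedness is coded as a separate attribute after the event has been collected.

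Carry the same wording into the case report form instructions, so that the four centres apply one rule and the monitors have something definite to check against. This is a recording rule only and alters no treatment procedure.

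The cost is a small text change, more minor local events to record, and possibly a higher reported adverse-event rate for moxibustion. The change does not remove the difference in the number of safety assessments between the groups, which will still have to be borne in mind when total rates are compared.

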#### **Participant protections and ethics**

To protect human participants, the protocol was written according to general ethical guidelines, such as the Declaration of Helsinki and Korean Good Clinical Practice and was approved by the institutional review board of each

trial centre (Daejeon University Hospital, Kyungwon University Gil Oriental Medical Hospital, Dongshin University Gwangju Oriental Hospital, and Semyung University Oriental Medicine Hospital). The Korea Institute of Oriental Medicine certified the ethics approval of the clinical centres as above. The study participant consent process includes information about potential risks, benefits, alternatives, and responsibilities during the trial. Before participants agree to participate in this trial, researchers will explain this information in detail in person.

#### **Discussion**

Moxibustion and acupuncture have been widely used to treat the pain and functional limitations of KOA in Korea [20]. Some trials [11-14,34] have been conducted to evaluate the effectiveness of moxibustion in treating KOA in Korea and China. Moxibustion and NSAIDs were compared in 3 RCTs [11-13], combination therapy (moxibustion plus NSAIDs) and NSAIDs were compared in 1 RCT [14], and moxibustion and a hot pack were compared in 1 RCT [34]. According to these trials, single or combination moxibustion therapies increased the total response rate and decreased symptoms of pain in KOA patients. However, the processes of random sequence generation and allocation concealment were not reported in 4 trials [11,13,14,34]. Moreover, none of the trials used valid and reliable assessment tools, such as the WOMAC, and assessor blinding was not described. It is therefore not possible to exclude the possibility of a high risk of bias and determine the effectiveness of moxibustion treatment for KOA.

Concealment is the most critical factor of the allocation process, and a high risk of bias is generated by unconcealed allocation [35,36]. In a recent well-designed systematic review of acupuncture for chronic pain, only RCTs that used an unambiguous method of allocation concealment were included [37]. Therefore, we designed our protocol with adequate methodology of random sequence generation and allocation concealment using validated assessment tools, such as the WOMAC, SF-36, and BDI, and monitors will regularly evaluate whether the trial is being conducted according to the planned protocol.

Mixed-method research is the most recent systematic approach of using 2 or more research methods to answer a single research question. This approach has the advantages of expanding the understanding of the procedure's effects and verifying results from another perspective compared to an approach using a single method because the supplemental component enhances the validity of the study [36,38]. This method has been used to determine the effectiveness of interventions in recent studies on complementary and alternative medicine [39-41]. To comprehensively understand the effectiveness of moxibustion for KOA patients, we will conduct not only a quantitative

data analysis but also economic and qualitative data analyses. A nested economic evaluation and qualitative research within a pragmatic clinical trial will be used as a mixed-methods approach to answer the question from various perspective on the reasons for using moxibustion for KOA.

One limitation of this study is the possibility of a high risk of bias regarding blinding because we will use usual care as a control instead of a sham procedure. One study [42] on functional constipation used sham moxibustion to blind participants to evaluate the efficacy of moxibustion, but a blinding test was not performed, and it is necessary to cover the eyes with a patch to successfully blind participants to the sham moxibustion device [43]. The researchers who designed this protocol agreed that it would be difficult to blind participants using any previously developed sham device [17,43,44], and that a sham device is difficult to use because of the high prevalence of moxibustion in Korea and there are technical challenges associated with developing a sham device. Additionally, it is more appropriate to use a pragmatic design to answer our research question, which is whether moxibustion treatment is effective in treating KOA in real practice. Therefore, we used the pragmatic approach of comparing treatment to usual care, permitting additional treatment points as well as standard treatment points, and using patient-centred outcomes in multiple centres.

This pragmatic randomised controlled trial using the mixed-methods approach may provide rigorous evidence for the effectiveness of moxibustion in treating KOA.

#### Competing interests

The authors declare that they have no competing interests.

#### Acknowledgements

This study is supported by the Development of Acupuncture, Moxibustion and Meridian Standard Health Technology (K11010) of the Korea Institute of Oriental Medicine.

**Submit your next manuscript to BioMed Central and take full advantage of:**

- **Convenient online submission**
- **Thorough peer review**
- **No space constraints or color figure charges**
- **Immediate publication on acceptance**
- **Inclusion in PubMed, CAS, Scopus and Google Scholar**
- **Research which is freely available for redistribution**

Submit your manuscript at  
www.biomedcentral.com/submit

[figure not shown]

Supplement: Protocol S1 — Published protocol of this study. (PDF) [file pone.0101973.s003.pdf]
